### Sample Size

#### Research Questions 1-3 (Participants: Older Adults)

As this is a feasibility study, a sample size calculation is not required [17]. However, we can estimate the number of participants we will be able to recruit during the data collection period. In this feasibility study with a statistical power of 0.8, an α of .05, and an effect size of 1.20, the minimum required sample size will be 24 participants in total (12 in each group [19]). We aim to recruit 15 participants for each group, for a total sample size of 30, to compensate for a 20% dropout rate. Sample size calculations are estimated using G*Power (version 3.1.9.4, Universitat Kiel) [29].

#### Research Questions 4-5 (Participants: Therapists)

We aim to recruit 5-10 therapists participating in the Short-Term Assessment, Rehabilitation, and Treatment Psychiatry Day Hospital program who provided the intervention.

### Recruitment

#### Participants (Older Adults)

An invitation to participate will be posted in the Short-Term Assessment, Rehabilitation, and Treatment Psychiatry Day Hospital program at Glenrose Rehabilitation Hospital. Therapists will support recruitment strategies, including the provision of information sessions and one-on-one conversations with potential participants. The first contact with a potential participant will be made through one of the therapists not involved in the research team. Therapists who are already involved in the clinical care of the patients will then determine the individuals’ willingness to be approached by the therapist researcher regarding participation and then obtain their consent for the study, as the case may be.

#### Allocation

##### Sequence Generation

Probability sampling will be used. Random sequence generation will be prepared in advance by a research team member ([name]) on an Excel file spreadsheet (RAND function) using permuted block randomization with a block size of 4 and a ratio of 1:1.

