### Study Setting

This study will be conducted at the Short-Term Assessment, Rehabilitation, and Treatment Psychiatry Day Hospital at Glenrose Rehabilitation Hospital located in Edmonton, Alberta, Canada.

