##### Implementation

If a potential participant meets the inclusion criteria, the therapist researcher ([name]) will ask the study coordinator to check whether a place is available in the study for that participant in a given group. If a place is available, then the therapist researcher ([name]), or another therapist involved in the recruitment process, will invite the participant to participate in the study, explain the study to him or her, and ask him or her to sign the consent form. If a potential participant is assigned to a particular therapist researcher ([name]), the therapist would not invite the participant to participate in the study. Instead, a secondary therapist researcher will do so. As a result, the freedom to decline will not be compromised. Once the participants or their substitute decision makers have signed the consent form and given their assent, the therapist researcher ([name]) will inform the study coordinator. The study coordinator will allocate each participant to 1 arm of the trial according to the allocation protocol and will assign a code. This code will be given to the therapist researcher ([name]) and research assistants (RAs) who will conduct the assessments.

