#### Blinding (Masking)

The assessments of outcome variables will be conducted by RAs who are blinded to the treatment allocation. Owing to the nature of the intervention, neither the participants nor the therapist can be blinded to the treatment allocation, but they are strongly encouraged not to disclose the participants’ allocation status during the assessments. An RA will enter the data into a computer on separate datasheets, and a senior RA will conduct the data analysis under the supervision of the principal investigator (PI; [name]).

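### A single published block size of 4 at one site with unblinded recruiting therapists leaves up to 31% of allocations deducible in advance; mixed undisclosed blocks would cut that ceiling to about 11%

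*Protocol article*

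**What the plan says.** All references are to the protocol article.

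- **Sequence Generation:** the list is prepared in advance "using permuted block randomization with a block size of 4 and a ratio of 1:1". No stratification factor is named, so I take it as a single sequence.
- **Study Setting:** there is one site, the psychiatry day hospital programme.
- **Recruitment and Implementation:** programme therapists make first contact. A therapist researcher or another recruiting therapist "will invite the participant to participate in the study, explain the study to him or her" and obtains consent. The study coordinator then allocates that participant and assigns a code, which goes to the therapist researcher and to the assessing research assistants.
- **Concealment Mechanism:** the randomization code is held back until patients are recruited and baseline measurements are complete.
- **Blinding (Masking):** "neither the participants nor the therapist can be blinded to the treatment allocation". The research assistants who assess outcomes are blinded.
- **Sample Size:** "We aim to recruit 15 participants for each group, for a total sample size of 30".

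**The concern.** Under permuted blocks of known, constant size, the next assignment can be worked out from the previous ones. In a 1:1 block of 4, the fourth assignment is always fixed by the first three, and the third is fixed whenever the first two agree. Keeping the list locked protects the list, but not against this inference.

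Three features of this trial make the inference possible in principle. The block size is public, there is one sequence at one site, and the people who recruit belong to the programme in which the arms are delivered openly. Allocation is described participant by participant, so earlier assignments exist while later patients are still being approached.

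What is at stake is selective enrolment: whom to approach, and when, could come to depend on the arm due next. Blinded assessors do not guard against that, and neither does a Mann–Whitney comparison. The study is also meant to test the design for a definitive trial, so a weakness in the allocation scheme could be carried forward.

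**Working it through.** **Inputs.** Block size 4, ratio 1:1 (Sequence Generation); 30 participants, 15 per group (Sample Size); one sequence (no strata named).

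**The plan's own figure.** The article gives no figure for predictability, so the only one to reproduce is the sample size. Its inputs are "with a statistical power of 0.8, an α of .05, and an effect size of 1.20". A two-sided two-sample t test needs 11.94 per arm, so 12 per arm and 24 in total. Power at 12 per arm is 0.802. Allowing for 20% dropout, 24 / 0.80 = 30. The stated 24 and 30 both reproduce.

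**Certain allocations, fixed blocks of 4.** There are 6 equally likely blocks.
- AABB and BBAA each make 2 assignments certain (the third and fourth).
- The other four (ABAB, ABBA, BABA, BAAB) each make 1 certain (the fourth).
- Mean per block = (2×2 + 4×1)/6 = 8/6 = 1.333, or 33.3% of assignments.
- 30 = 7×4 + 2, and neither of the two places used in the eighth block can be certain.
- Total = 7 × 1.333 + 0 = 9.33 of 30 = **31.1%**, with a range of 7 to 14 participants. A simulation of 20,000 sequences gave 31.1%.

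**Best guess, fixed blocks of 4.** The chance of being right at each place is 0.5, 0.667, 0.667 and 1, which sums to 2.833 per block. Over 30: (7 × 2.833 + 0.5 + 0.667)/30 = 21.0/30 = **70%**, against 50% by chance.

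**Three blocks of 4 and three of 6 in random order.** Total = 3×4 + 3×6 = 12 + 18 = 30. Every block is balanced, so the split is 15:15. I simulated 20,000 sequences with a recruiter who knows the mix but not the order, and who updates after every allocation seen.
- Certain allocations: 3.3 of 30 = **10.9%**.
- Best guess right: **69%**.
- Relative fall in certain allocations: (31.1 − 10.9)/31.1 = 65%, about two thirds.

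**Running imbalance.** The largest difference between arms within a block is half the block size: 4/2 = 2 now, 6/2 = 3 with the mix.

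**Lower end of the range (illustration).** Assume consent near week 0 and even accrual. The 8-month data collection period is about 35 weeks. Less 18 weeks per participant, that leaves about 17 weeks to enrol 30. Four consecutive recruits then span 4 × 17/30 = 2.3 weeks. The videos start only after the week-12 measurement. If that is when the arm first shows, a block is complete long before any of its arms is visible, and the certain share approaches 0. If consent falls near week 12, or recruiters learn the arm at allocation, it moves towards 31%.

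**Side point: the final split.** With 7 full blocks plus 2 places, the first two places of the eighth block agree with probability 2/6 = 1/3, which gives 16:14. Power at an effect size of 1.20 is 0.886 for 16:14 and 0.887 for 15:15.

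**The case against.** The strongest reply is that 31% depends on a premise the article does not state: that each recruiter sees every earlier arm, in order, before the next invitation. Several details point the other way.

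- The code given to the therapist researcher also goes to assessors who are said to be blinded. It may therefore be a participant number that reveals no arm.
- The videos begin after week 12 and are shown to groups of up to 5, not one person at a time in list order.
- Recruitment is spread over several people.

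This objection stands as far as it goes: 31% is a ceiling. It does not remove the point. The article does not say when recruiters learn the arm, and withholding the list is not by itself a defence against deduction. One could read the concealment paragraph as meaning that nobody is allocated until everyone is enrolled, which would close the gap, but Implementation describes allocation after each consent.

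A second objection is that the remedy hardly changes best-guess accuracy. That is correct. The gain is confined to certain foreknowledge.

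A third is that a 16:14 split is harmless and that 15 per group is only an aim. That is also correct. A reader might infer that the design fails to deliver a promised balance, but the article promises none and the power cost is about 0.1 percentage point.

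A reader might also infer, from the use of a spreadsheet random function, that the list cannot be audited. The article says the sequence is prepared in advance and does not say that the values stay live. That kind of detail is commonly left to fuller documents, so no finding rests on it.

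**Conclusion.** The point holds as a modest, inexpensive improvement to consider. Fixed, published blocks of 4 give weaker protection than this open, single-site setting could easily have. Worst-case certain foreknowledge is 9.3 of 30 allocations (31%), and the practical share lies between near 0 and 31%. The ceiling assumes one unstratified sequence, exactly 30 allocated, a known block size, and all earlier arms seen in order.

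A reader might go further and infer that recruiters will know 3 in 10 allocations, or that the treatment comparison is biased by a definite amount. The documents support neither. For example, suppose participants steered into known places differed by 0.5 SD between arms. The spurious difference at the ceiling would then be 0.311 × 0.5 = 0.16 SD. With 0.2 or 0.8 SD instead, it would be 0.06 or 0.25 SD, and with no visibility it would be 0. Nothing in the article fixes the degree of steering or the visibility, so these figures only illustrate the scale.

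**What to change.** Before recruitment resumes, replace the unused part of the list with permuted blocks of 4 and 6 in random order. For a full new list, use three of each, which gives exactly 30 and 15:15. If some participants have already been allocated, choose a mix of 4s and 6s that completes 15:15. Keep the block sizes from recruiting therapists until allocation is complete, and amend the sequence-generation text to say that sizes vary and are withheld.

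The cost is about an hour's work and a sentence in the protocol. The downside is a largest running imbalance of 3 instead of 2.

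One related item is not solved by changing the blocks. Implementation has the therapist researcher ask, before inviting a patient, whether a place is open in a particular group. The same amendment could state that this check reveals nothing about the coming arm.

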##### Concealment Mechanism

Allocation concealment will be ensured, as we will not release the randomization code until the patients have been recruited to the trial and all of the baseline measurements have been completed.

##### Implementation

If a potential participant meets the inclusion criteria, the therapist researcher ([name]) will ask the study coordinator to check whether a place is available in the study for that participant in a given group. If a place is available, then the therapist researcher ([name]), or another therapist involved in the recruitment process, will invite the participant to participate in the study, explain the study to him or her, and ask him or her to sign the consent form. If a potential participant is assigned to a particular therapist researcher ([name]), the therapist would not invite the participant to participate in the study. Instead, a secondary therapist researcher will do so. As a result, the freedom to decline will not be compromised. Once the participants or their substitute decision makers have signed the consent form and given their assent, the therapist researcher ([name]) will inform the study coordinator. The study coordinator will allocate each participant to 1 arm of the trial according to the allocation protocol and will assign a code. This code will be given to the therapist researcher ([name]) and research assistants (RAs) who will conduct the assessments.

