#### Intervention Group (Participants: Older Adults)

Research questions 1-2 (primary outcome variables): at the enrollment of the program (week 0 [T_0_], called the pretest program enrollment), the pretest before starting showing the videos (week 12 [T_1_]), and at the posttest when the participants finish the program and watch the videos (week 18 [T_8_]).

Research questions 1-2 (secondary outcome variables): after watching each video, that is, weeks 13-17 (T_1-7_).Research question 3 (participants, older adults): after watching every video (week 18 [T_8_]).

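### The implementation text checks for a place in a given group before consent and allocates at consent; both conflict with the stated concealment rule and can undermine it.

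*Protocol article*

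**What the plan says.** All references are to the protocol article.

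- **Allocation, Implementation.** Once a patient meets the inclusion criteria, the therapist researcher "will ask the study coordinator to check whether a place is available in the study for that participant in a given group". The next step is conditional: "If a place is available, then the therapist researcher" or another recruiting therapist makes the invitation and seeks consent. Allocation comes next: "Once the participants or their substitute decision makers have signed the consent form and given their assent", the coordinator is told, and "The study coordinator will allocate each participant to 1 arm of the trial according to the allocation protocol and will assign a code". That code goes to the therapist researcher "and research assistants (RAs) who will conduct the assessments".
- **Allocation, Concealment Mechanism.** Concealment is said to be ensured because "we will not release the randomization code until the patients have been recruited to the trial and all of the baseline measurements have been completed".
- **Allocation, Sequence Generation.** The list is prepared in advance, "using permuted block randomization with a block size of 4 and a ratio of 1:1".
- **Participant Timeline.** The primary outcomes are measured at week 0 (T0, labelled a pretest at program enrollment), at week 12 (T1) and at week 18 (T8). For the intervention group, T1 is described as "the pretest before starting showing the videos (week 12 [T_1".

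**The concern.** A patient who has not been randomised has no arm. Under concealment, the recruiter therefore needs to know only whether the trial is open. A question about a place for this patient in a particular group invites an answer that depends on the arm, and that answer decides who is invited. This is the route by which selection bias enters: suitable patients can be held back or put forward according to which arm has room.

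The second issue is timing. One section makes completed baseline measurement the condition for release, and the other makes consent the trigger for allocation. If participants learn their arm at consent, the T1 scores may be given with that knowledge. GAD-7, PANAS and OPQoL-Brief are self-reports, so blinding the assessor does not protect them.

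With 15 people per arm and between-group comparisons by Mann-Whitney test, a few selectively invited patients could shift the result, and that test does not adjust for it. The trial also asks whether this protocol is feasible for a definitive trial, so the enrolment procedure itself may be carried forward.

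**Working it through.** The plan gives no figure on this point. The check compares the sections and adds one short calculation on predictability.

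**1. What the place check can reveal.** The article uses group in more than one sense, so each reading needs its own answer.

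| Reading of group | Source | What the recruiter's answer carries |
|---|---|---|
| Trial arm | Interventions (experimental or control group) | Invitation depends on the arm before consent |
| Video session, at most 5 people, checked only when the next assignment is to video | Experimental (Intervention) Group | The fact of the check reveals the arm |
| Video session, checked for every candidate alike | Same | Nothing about the next assignment |
| Therapy group common to both arms | Control Group | Nothing about the arm |

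Two readings open a route to selection and two do not. The text does not choose between them. The first is the natural reading, because the sentence stands in the allocation section.

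**2. The order of steps.**

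- Implementation: eligibility, place check, invitation, consent, allocation and code, code passed to therapist and assessors. No measurement appears between consent and allocation.
- Concealment Mechanism: recruitment, all baseline measurements, release of the code.
- Timeline: two pre-intervention measurements, T0 at week 0 and T1 at week 12, both labelled pretests. All baseline measurements therefore most naturally includes T1.

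The consent week is not given. If consent and disclosure both fell in week 0, the arm would be known for 12 − 0 = 12 weeks before T1. This is an upper bound. With consent close to week 12 the gap would be short.

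**3. How much a leak would matter with fixed blocks of 4.** Assume that the recruiter knows all past assignments and always guesses the arm with more places left. Over the 6 equally likely orderings of two and two:

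- Position 1: 1/2 correct.
- Position 2: 2/3 correct, since two of the three remaining places belong to the other arm.
- Position 3: the first two are equal with probability 1/3 (then certain) and differ with probability 2/3 (then 1/2), so 1/3 + 2/3 × 1/2 = 2/3.
- Position 4: always certain, 1.

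The sum is 0.500 + 0.667 + 0.667 + 1 = 2.833 of 4, or 70.8%. For 30 people (seven full blocks and two more), it is 7 × 2.833 + 0.500 + 0.667 = 21.0, and 21.0/30 = 70.0%. Chance gives 50%.

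Assignments known with certainty: position 4 always and position 3 with probability 1/3, so 1.333 of 4, or 33.3%. This also requires knowing the block size and where blocks start.

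**4. Would varying block sizes help?** With blocks of 2, 4 and 6 equally likely, expected correct guesses are 1.5 of 2, 2.833 of 4 and 4.1 of 6. Together this is (1.5 + 2.833 + 4.1)/12 = 8.433/12 = 70.3%. The best-guess rate hardly moves from 70.8%, because the guess uses only the running imbalance. What varying sizes reduce is certain knowledge of the next assignment.

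**The case against.** The strongest reply is that nothing here shows a breach. Implementation does not say that the coordinator discloses the next assignment, and it places allocation after consent. A capacity check applied to everyone is harmless, since anyone who might be randomised to video needs a possible place. Allocation at consent is compatible with the concealment rule if the coordinator allocates and withholds the result. The code may be no more than the numerical participant code described under Confidentiality. It is handed to research assistants whom the Blinding section calls blinded, so it may well not show the arm. Allocating after consent but before a later measurement is also not a failure of concealment, which concerns knowledge before enrolment. Finally, the trial's stated primary objective is feasibility.

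Most of this stands as a limit on the claim. A reader might infer that concealment is defeated, or that participants certainly know their arm before T1. The documents support neither: group is ambiguous, the consent week is not given, and baseline is not defined as T0, T1 or both. The 70.8% and 33.3% depend on knowledge that the article does not say recruiters have. If release does wait for T1, the assignments of patients still before week 12 are unknown to recruiters.

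The reply does not remove the sentence that makes invitation depend on a place in a given group, or the mismatch between the two sections on what must happen before allocation is released. Both are in the text, and a site following Implementation literally could depart from the rule on which the concealment claim rests.

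**Conclusion.** The implementation text is inconsistent with the concealment statement and can undermine it. Two points hold:

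1. Before consent, invitation depends on a place in a given group. This opens a route to selection by arm if group means the arm, or if it means a video slot checked only for some candidates.
2. Allocation is triggered by consent with no baseline step named, whereas release of the code is elsewhere tied to completion of all baseline measurements.

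The second point is a contradiction in timing that puts T1 at risk as an unbiased pretest. It is not in itself a concealment failure. The size of any bias cannot be derived from the documents. The bounds are up to 12 weeks of knowledge before T1, if consent and disclosure occur in week 0, and about 70% correct guesses, if past assignments are known. The fixed block of 4 is secondary.

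This should be fixed, with moderate confidence, because the harmful reading is the natural one but not the only one.

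**What to change.** - **Place check.** Remove the reference to a given group. The recruiter may ask only whether the trial is open. If video capacity must be checked, the check should be identical for every candidate and made without reference to the randomisation list.
- **Order.** Rewrite Concealment Mechanism and Implementation as one sequence: eligibility, consent, all pre-intervention measurements including T1 at week 12, then disclosure of the next assignment by the coordinator. Define baseline accordingly. State whether the code given to the therapist and assessors is the participant number or reveals the arm.
- **Optional.** Keep the block size from recruiting therapists. Varying block sizes would reduce certain knowledge of the next assignment but leaves the best-guess rate at about 70%, so it does not replace the first two changes.

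The cost is mainly protocol wording. The practical downsides are shorter notice for scheduling video groups, and that people who leave before week 12 are not randomised. The article reports recruitment on hold as of August 2021, so the natural moment is before it resumes. Concealment cannot be restored once patients have been enrolled.
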